## Methods

### Design

To study the effects of R&W an RCT design is implemented in the 7th Grade of preparatory vocational education level. Schools from different parts of The Netherlands are randomly assigned to one of three intervention groups or to the control group (Fig. 1). In the ‘Light’ condition a core team of teachers is trained with the three-day training course to become certified R&W trainers and implement the R&W program. In the ‘Standard’ condition a core team is trained to become R&W trainers and the rest of the school-team that teaches 7th Grade students follows a three-day training to learn how they can support the R&W trainers of their school and how they can apply R&W in their regular classes. The ‘Plus’ condition is equal to the ‘Standard’ condition with the addition of a parent component. The parents watch a documentary of R&W, get an invitation to join a lesson in the school, receive weekly e-mails with information about the lesson of that week and are stimulated to act on this information, for instance by communicating about R&W or using R&W language. This will not only create a supporting environment within the school, but also in students’ homes. In the control condition students receive CAU; i.e., current school policy to enhance socio-emotional adjustment and social safety of students.

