### Recruitment

Schools were recruited through the network of the developers of R&W, the Gadaku Institute. An e-mail to certified R&W trainers was sent with information about this study and a message on the private R&W online forum was posted. Trainers asked within their network whether schools that did not implement R&W were interested in participating in this study. When schools were interested they contacted the Gadaku Institute which referred the school to the researchers. The researchers established whether the school was eligible for participation. If the school was eligible, the researcher provided additional information to the schools based on which the school made a decision concerning participation.

Schools were randomly assigned (1:1:1:1 ratio) by stratified block randomization, with blocks of four (i.e., the number of conditions in this study). Schools were stratified by school size (small to moderate sized schools: < 100 students in 7th Grade, large sized schools: > 100 students in 7th Grade) to establish a more equal distribution of students over the four conditions. The randomization numbers were generated by a random number generating computer program.

Students, parents, teachers, and R&W trainers received an information letter to inform them about R&W and the study. Parents also attended a parent-teacher evening where they received additional information about R&W. Students gave active informed consent and parents passive informed consent for participation of the student. Parents gave active informed consent for their own participation in the study. Active informed consent was also acquired for participation of teachers and R&W trainers.

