#### Mediators

Self-control is assessed with the Self-Control Scale short version [45] completed by the student. It contains 11 items (e.g., “I wish I had more self-discipline.”). This questionnaire measures students’ ability to change their inner responses, interrupt undesired behavioral impulses and abstain from acting on these tendencies. Additionally, halfway the questionnaire students complete a shortened version (19 items) of a delayed discounting computer task to measure self-control including a ‘catch’ question [46–48]. Students can choose a smaller, immediate reward or a larger, delayed reward (e.g., “Would you prefer to receive €54 today or in 117 days €55?”). To ascertain that the students have read the questions, a catch question is added, similar in form, amount and delay: “Would you prefer to receive €59 today or in 139 days €21?”

Self-reflection will be reported by the students using the Engage in reflection subscale of the Self-Reflection and Insight Scale [49]. It contains 6 items (e.g., “I don’t often think about my thoughts.”).

Self-esteem will be measured with the subscale Global self-perception of the Self-perception Profile [50] reported by the students. This subscale contains 5 items (e.g., “I’m often disappointed in myself.”).

Emotion regulation is measured using the subscales Impulse control (6 items; e.g., “When I’m upset, I feel out of control.”) and Strategies (8 items; e.g., “When I’m upset, I believe that I will remain that way for a long time.”) from the Difficulties in Emotion Regulation Scale [51] completed by students. These subscales measure students’ ability to control their emotional impulses and the regulation strategies they apply.

Deviant and prosocial communication is assessed using video-observations of same-sex dyads of classmates in a subsample of students in the ‘Standard’ and control condition. This observation task is based on the Peer Interaction Task [52]. The dyads plan an activity together, as warm-up, and subsequently discuss 3 situations concerning daily school situations. Each of these 4 segments lasts 5 min. The 20 min interactions are videotaped and coded. Deviant and prosocial communication is coded based on the Conversation Topic Code [53, 54] and communication ratings [55–57].

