#### Statistical analyses

The power calculations are based on the N:q rule for structural equation models [59]. This rule states that for each free parameter (q) 10 to 20 participants (N) are needed. We took the conservative approach by taking 20 participants per free parameter for our power calculations. In our multigroup LGC model there are 9 free parameters per condition, 36 free parameters in total. Thus a total sample of 720 participants is needed for our analysis, 180 participants in each condition. Since not only students can drop out but also classes (about 20 students) and schools (about 60 to 90 students), we will include three to four schools per condition. Missing data will be handled in M*plus*.

In our data, students are nested in classes which are nested in schools. Therefore, we will examine whether there is significant intra-class correlation on one of the levels (i.e., school, and class) and we will calculate the design effect. Each level with a design effect larger than 2.0 will be modeled in the analyses which allows us to correct for the nested data, that is multilevel analyses [60].

The first aim is to examine the effectiveness of R&W in the conditions which differ in the number of parties involved in the intervention. This will be examined using an analysis of covariance (ANCOVA) for the outcomes of socio-emotional adjustment and social safety, in case the design effect is smaller than 2.0. The dependent variables will be the post-measurements after the second year (8th Grade), the independent variables the condition, and the covariates the premeasurements (7th Grade). If needed, due to large design effects, multilevel regression analyses will be used (This also holds for the other aims). Then, we will analyze the trajectories of change in socio-emotional adjustment and social safety during R&W with multigroup Latent Growth Curve (LGC) modeling in M*plus*. We will examine if these trajectories of change differ significantly between the four conditions.

The second aim, the effect of potential moderators on the effectiveness of R&W on socio-emotional adjustment and social safety, will be examined using ANCOVAs for categorical moderators and regression analyses for the continuous moderators. The interaction effects of the concerned outcome measure with the student, trainer or parent characteristics will be added as an interaction term.

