The third aim, studying the working mechanisms of R&W, will be examined by analyzing multiple mediators. We will analyze whether the R&W intervention improves students’ self-control, self-reflection, self-esteem and emotion regulation by performing ANCOVAs. Furthermore, we will analyze whether the change in these concepts mediate the relation between R&W and socio-emotional adjustment and social safety through LGC modeling in M*plus*. We will model the mediators as well as the outcome measures in this mediation analysis on the assessments before, during, and after R&W [61]. Furthermore, we will study whether R&W decreases deviant communication and increases prosocial communication. We will analyze if changes in deviant and prosocial communication are mediators of the effect of R&W on social safety. We will model these indirect effects in M*plus* using bootstrapping.

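### School, the randomised unit, stays in the analysis only if its estimated design effect exceeds 2.0, so tests of condition can exceed their nominal type I error

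*Protocol article*

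**What the plan says.** The unit of allocation is clear. Under Recruitment: "Schools were randomly assigned (1:1:1:1 ratio) by stratified block randomization, with blocks of four". Under Design: "Schools from different parts of The Netherlands are randomly assigned to one of three intervention groups or to the control group".

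The Statistical analyses section recognises the hierarchy ("students are nested in classes which are nested in schools"). It plans to examine the ICC at school and class level and to calculate design effects, and then sets the rule: "Each level with a design effect larger than 2.0 will be modeled in the analyses". The main effectiveness analysis is an ANCOVA of the post-measurement after the second year, adjusted for the pre-measurement, "in case the design effect is smaller than 2.0". Multilevel regression replaces it only when design effects are large, and the same switch is stated to apply to the other aims.

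The section gives about 20 students per class, about 60 to 90 per school and three to four schools per condition. It states no significance level and no ICC. Nothing in the article keeps school in the model regardless of the estimate, or provides another allowance for clustering when the limit is not reached.

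**The concern.** Condition is a property of the school. The precision of any comparison between conditions therefore depends on how much outcomes vary between schools, and that variance belongs in the standard error whether or not a preliminary estimate looks large. The plan lets it be removed on the strength of an estimate from 12 to 16 schools. If it is removed while the true school ICC is above zero, the standard error is too small and the p-value too optimistic.

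At stake is the main conclusion. Rock and Water, or one of its more intensive variants, could be declared effective because a few schools happen to differ. Because the rule extends to all aims, the moderator and mediator analyses share the exposure.

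**Working it through.** **Inputs from the protocol article.** School randomised to four conditions (Design, Recruitment); 720 students, 180 per condition; 9 free parameters per condition, 36 in total, 20 participants each; about 20 students per class, 60 to 90 per school; 3 to 4 schools per condition (Statistical analyses).

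**Assumptions.** Two-sided 5% level; true design effect (DE) varied from 1.0 to 3.0, because no ICC is given.

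**Step 1: the plan's own figure.** 20 × 9 = 180 per condition and 20 × 36 = 720 in total. This reproduces exactly. The calculation contains no alpha, effect size, ICC or design effect, so it holds no margin for clustering.

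**Step 2: what a design effect of 2.0 means.** DE = 1 + (m − 1) × ICC, so DE = 2.0 at ICC = 1/(m − 1).

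- m = 45 (180/4 schools): 1/44 = 0.023
- m = 60 (180/3 schools): 1/59 = 0.017
- m = 90: 1/89 = 0.011

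Effective sample at DE 2.0: 720/2 = 360. An analysis that ignores it has standard errors 1/√2 = 0.71 times the correct size, about 29% too small.

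**Step 3: fixed case, clustering always ignored.** Pairwise error = 2 × (1 − Φ(1.96/√DE)); four-condition error = P(χ² on 3 df > 7.815/DE).

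| True DE | Pairwise | Four-condition |
|---|---|---|
| 1.25 | 8.0% | 10.0% |
| 1.5 | 11.0% | 15.7% |
| 1.9 | 15.5% | 25.0% |
| 2.0 | 16.6% | 27.2% |

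These figures describe plain ANCOVA at a known design effect, not the planned rule.

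**Step 4: the two-step rule.** Null simulation, 6000 runs per setting; 4 conditions × 3 schools × 60 students, or × 4 schools × 45 students; school-level clustering only, no covariate. If the estimated DE is at most 2.0, students are analysed directly; otherwise condition is tested against between-school variation on 4 × (3 − 1) = 8 or 4 × (4 − 1) = 12 df. Ranges cover the two layouts.

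| True DE | Estimated DE ≤ 2.0 | Rule, pairwise | Rule, four-condition |
|---|---|---|---|
| 1.0 | 97.9–99.1% | 4.6–5.3% | 4.5–4.7% |
| 1.25 | 91.1–93.8% | 6.6–6.7% | 7.2–7.9% |
| 1.5 | 80.7–83.5% | 6.9–8.2% | 8.5–10.5% |
| 1.9 | 61.2–61.9% | 8.5–8.7% | 10.0–11.1% |
| 2.0 | 54.0–56.0% | 7.5–8.2% | 9.2–11.1% |
| 3.0 | 17.0–23.0% | 6.4–6.5% | 7.1–7.6% |

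Monte Carlo standard error near 5% is √(0.05 × 0.95/6000) = 0.3 percentage points. Always testing at school level gave 4.3–5.4% (pairwise) and 4.7–5.4% (four-condition) at every design effect tried. Among runs sent to plain ANCOVA at a true DE of 1.9 to 3.0, error was 10–13% (pairwise) and 13–18% (four-condition).

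**Step 5: sensitivity to simulation choices.** Two further simulations (4000 runs per setting) added three classes of 20 per school, with assumed school variance shares of 0.005–0.02 and class shares of 0.01–0.03. One gave 6.5–9% and 7.5–11%. The other, estimating the ICC within conditions, gave 8–10% and 12–16%. Both returned about 5% when the test was always at school level. The way the ICC is estimated may explain the difference, and the article does not fix it.

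**The case against.** The strongest defence is that the plan does not ignore clustering. It examines it at both levels and moves to multilevel models when the design effect is large. The inflation is therefore conditional: it vanishes if the school ICC is zero, and a large chance difference between schools tends to push the estimate over 2.0 and into the multilevel branch. That is why the error in Step 4 is well below that in Step 3. Adjustment for the pre-measurement may also lower the residual ICC, and the Step 4 simulation has no covariate. All of this stands and limits the size of the problem. It does not remove it, since baseline adjustment does not guarantee a residual school ICC of zero.

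Several stronger readings are tempting but not supported:

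- **Every standard error for condition is too small.** This is true only where school is dropped and its true ICC is above zero.
- **School and class can each sit just under the limit and together hide a much larger effect.** This depends on computing the school design effect from the school-only variance share. The article does not say so; a students-in-schools estimate would absorb class variance and usually trigger the rule.
- **The rule can never act for the video mediators.** These come from "video-observations of same-sex dyads of classmates in a subsample of students". The class and school levels still apply to them. Dependence within pairs matters only if scores are given per student, which the article does not state.
- **The bootstrap resamples students, or the multilevel branch uses large-sample z-tests.** "We will model these indirect effects in M*plus* using bootstrapping" does not name the resampling unit, and no estimator is given. Such detail is commonly left to the analysis plan.

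**Conclusion.** The point holds as a fault in a stated rule, not as a missing detail. The randomised level can be dropped from the test of condition on a noisy estimate, and the tolerated design effect of up to 2.0 is too large to disregard. Under an assumed nominal 5% level and true design effects of about 1.25 to 3, overall type I error is roughly 6–9% for a pairwise contrast and 7–11% for the four-condition test, with 16% the highest value in any simulation of the rule. The fixed worst case for a pairwise contrast, if a true design effect of 2.0 is ignored, is 16.6%. At an ICC of zero there is no inflation. Alpha and the ICC range are assumptions, because the article gives neither; the direction of the error does not depend on them.

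**What to change.** Remove the design-effect threshold for school. State that every ANCOVA or regression test of condition keeps school in the model whatever the estimated ICC, with inference suited to 12 to 16 schools: for example a random school effect fitted by REML with Kenward-Roger or Satterthwaite degrees of freedom, or an analysis of adjusted school means on 8 to 12 df. Report ICCs and design effects as descriptive results only.

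For the latent growth curve and mediation models this does not transfer directly: with 9 free parameters per condition and three to four schools in each, full school and class random effects are hardly estimable. Either name a method of accounting for school clustering that is feasible with so few schools, or label the condition comparisons from these models as exploratory. If video scores are per student, allow for dependence within pairs as well.

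For the ANCOVA and regression analyses the cost is a change of wording, wider confidence intervals and some loss of nominal power. The degrees of freedom alone widen a 95% interval by about 18% at 8 df (2.31/1.96) or 11% at 12 df (2.18/1.96), before between-school variance is added. The growth-curve and mediation analyses need more work.

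### Schools are randomised, but school enters the model only if its estimated design effect exceeds 2.0, so the error term for condition effects can be left out on a noisy estimate

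*Protocol article*

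**What the plan says.** The unit of randomisation is clear. Under Design: "Schools from different parts of The Netherlands are randomly assigned to one of three intervention groups or to the control group". Under Recruitment: "Schools were randomly assigned (1:1:1:1 ratio) by stratified block randomization, with blocks of four". The Statistical analyses section plans three to four schools per condition, with about 20 students in a class and 60 to 90 in a school.

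That section acknowledges the hierarchy ("In our data, students are nested in classes which are nested in schools") and then sets the rule: "Each level with a design effect larger than 2.0 will be modeled in the analyses which allows us to correct for the nested data". For the first aim the default is an ANCOVA of the post-measurement on condition and pre-measurement, to be used "in case the design effect is smaller than 2.0". If design effects are large, "multilevel regression analyses will be used (This also holds for the other aims").

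The section also says it will look at whether the intraclass correlation at school or class level is significant, without saying what part that plays in the decision. Nothing in the article keeps school in the model because it was the randomised unit.

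**The concern.** All students in a school share one condition, so a difference between conditions is a difference between sets of schools. Its standard error has to reflect how much schools vary. A student-level ANCOVA replaces that variation with variation between students and treats 180 students per condition as independent.

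The rule treats a design effect below 2.0 as negligible. For a comparison of randomised schools it is not: at 2.0 the true variance of a condition mean is twice what the single-level analysis assumes. The deciding quantity is also estimated from only 12 to 16 schools, so chance largely settles whether school is kept, and the trials in which it is dropped include many where it matters.

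At stake are the p-values and intervals for the first aim, and for the effects of R&W on the mediators in the third. Ordinary differences between schools could be reported as effects of R&W, and the Discussion says that a positive result would be used to stimulate implementation.

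**Working it through.** **Inputs from the article.** Four conditions; three to four schools per condition, so 12 to 16 in all; about 20 students per class and 60 to 90 per school; 180 students per condition.

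**Assumptions, because the article gives no figure.** Two-sided alpha of 0.05, and a range of school ICCs.

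**The plan's own figure.** The article states no false-positive rate, so there is none to reproduce. Its sample size does reproduce: 20 × 9 = 180 per condition and 20 × 36 = 720. It contains no design effect, and this point does not change it. With 180 per condition, three schools give 180/3 = 60 students each and four give 180/4 = 45.

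**Step 1: what the threshold means.** Design effect DE = 1 + (m − 1) × ICC, so DE = 2.0 at ICC = 1/(m − 1).
- m = 45: 1/44 = 0.023
- m = 60: 1/59 = 0.017
- m = 90: 1/89 = 0.011

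**Step 2: false-positive rate when school is ignored.** Two conditions: 2 × [1 − Φ(1.96/√DE)]. Four-condition test on 3 df: P(χ²₃ > 7.815/DE).

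| True DE | Two conditions | Four-condition test |
|---|---|---|
| 1.0 | 5.0% | 5.0% |
| 1.25 | 8.0% | 10.0% |
| 1.5 | 11.0% | 15.7% |
| 1.75 | 13.8% | 21.5% |
| 2.0 | 16.6% | 27.2% |

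At 2.0 these are 16.6/5 = 3.3 and 27.2/5 = 5.4 times nominal. Twice nominal is reached at DE 1.42 (two conditions) or 1.25 (four). Six times nominal would need DE 3.58 or 2.13, both above the cut-off.

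**Step 3: the two-step rule as a whole.** Simulation with no R&W effect, no pre-score and no class effect, 40,000 runs per setting. When the rule keeps school, a test against school-level error is credited. The article does not say whether the ICC is estimated within conditions or across all schools, so both are shown (within / across). Error rates are given as two-condition; four-condition.

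| Schools × students per condition | School ICC (DE) | School dropped | Error when dropped | Error over all trials |
|---|---|---|---|---|
| 3 × 60 | 0.010 (1.59) | 74% / 76% | 12.0; 18.0% / 8.5; 10.7% | 9.0; 13.3% / 7.6; 9.2% |
| 3 × 60 | 0.017 (2.00) | 57% / 56% | 16.8; 27.3% / 10.2; 13.0% | 10.0; 15.6% / 7.9; 9.4% |
| 3 × 60 | 0.020 (2.18) | 50% / 48% | 18.9; 31.3% / 10.7; 14.0% | 9.9; 15.7% / 7.8; 9.2% |
| 4 × 45 | 0.010 (1.44) | 84% / 86% | 10.2; 14.4% / 8.5; 10.8% | 8.7; 12.1% / 8.0; 10.0% |
| 4 × 45 | 0.020 (1.88) | 62% / 62% | 15.1; 25.1% / 10.4; 14.8% | 9.8; 15.6% / 8.3; 11.3% |

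A second simulation, with schools of 60 in three classes of 20 and class ICCs of 0 to 0.02, gave 7–10% and 8–15% over all trials. Taken together the ranges are about 7–10% (two conditions) and 8–16% (four-condition test). With school ICC zero the rule gives about 5%.

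At ICC 0.02 with 60 per school the true design effect already exceeds the cut-off, yet school is dropped in about half of trials.

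**Step 4: after the fix.** With school always in the model (12 − 4 = 8 or 16 − 4 = 12 df), simulated error is 4.8% to 5.3% at every ICC tried, from 0 to 0.05.

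**The case against.** The strongest reply is that the plan recognises the nesting, follows a cited convention and promises multilevel analysis where needed. That does not help here, because need is defined by the threshold, and the threshold does not ask which level was randomised. Nor is this detail left to a fuller document: the rule is stated.

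Other objections do stand and limit the point.

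- **A fixed multiplier.** A reader might infer that the plan inflates false positives two- to sixfold. The article gives no ICC or alpha, inflation is nil if schools do not differ, and sixfold needs a true design effect above 2.0.
- **Both levels dropped.** Class and school might each sit just under 2.0. A joint value of 1 + 19 × (1/19) + 59 × (1/59) = 3.0, with error of 26% and 46%, follows only if the ICCs come from a three-level decomposition. In a one-way analysis by school, the school ICC already contains (19/59) of the class ICC, so the school design effect is itself the joint figure. The article does not say which method is meant. If class is modelled and school is not, part of the excess is absorbed.
- **Outcome-by-outcome switching.** This is plausible, but the article does not state it.
- **Baseline adjustment.** The ANCOVA includes the pre-measurement and the simulations do not. If pre-scores absorb school differences and the rule uses unadjusted ICCs, the inflation is smaller than shown.
- **Second aim.** Interactions of condition with student gender, ethnicity or personality are estimated largely within schools, so these error rates do not carry over to them.

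**Conclusion.** The concern holds for tests of condition effects: the rule as written can leave out the randomised unit and then gives standard errors that are too small. Confidence in the defect is high; its size is conditional.

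At an assumed alpha of 0.05, ignoring school raises the error from 5% at a true design effect of 1 to about 17% (two conditions, about 3 times nominal) or 27% (four-condition test, about 5 times nominal) just below 2.0. The overall rate for the two-step rule is roughly 1.4 to 3 times nominal at school ICCs of about 0.01 to 0.02, in scenarios without the pre-score. The documents do not support an unconditional multiplier, or the same figures for within-school interactions. The rule should be changed before the conditions are compared.

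**What to change.** Remove the 2.0 threshold for school. State that every test of a condition effect (the first aim, and the effects of condition on mediators in the third) includes school as a random effect, or is done on school means adjusted for the pre-score, whatever the ICC or design effect. Base small-sample degrees of freedom on the number of schools in that comparison: about 8 to 12 for the four-condition comparison. The video-observation subsample covers only the Standard and control conditions, so at most 6 to 8 schools and 4 to 6 degrees of freedom. The threshold may stay for deciding whether class is added below school, and ICCs can be reported descriptively.

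The cost is analysis text and no new data. The text must also say how school is handled in the four-group growth-curve model, where three to four schools per group leave little information for a school random effect. The real price is wider confidence intervals and few degrees of freedom for outcomes that would otherwise have been analysed as if students were independent.

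### Schools are randomised within size strata, but the stated aim-1 model omits the stratum; if size predicts outcome, a school-level SE is overstated and whole-school loss can shift the contrast

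*Protocol article*

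**What the plan says.** Under Recruitment: "Schools were randomly assigned (1:1:1:1 ratio) by stratified block randomization, with blocks of four". "Schools were stratified by school size" in two classes, below and above 100 students in 7th Grade. The stated reason is "to establish a more equal distribution of students over the four conditions".

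Under Statistical analyses, the first-aim ANCOVA takes the measurement after the second year as dependent variable, with "the independent variables the condition, and the covariates the premeasurements (7th Grade"). That ANCOVA applies when the design effect is below 2.0. Otherwise: "If needed, due to large design effects, multilevel regression analyses will be used". The rule for clustering is "Each level with a design effect larger than 2.0 will be modeled in the analyses". No school-size term is named for either model, nor for the mediator ANCOVAs or the growth models.

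The same section expects that students, classes and whole schools (about 60 to 90 students) may drop out, and plans for this: "we will include three to four schools per condition". That makes 12 to 16 schools in total.

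**The concern.** Stratified randomisation forces the size classes to be balanced across conditions. Any outcome difference between large and small schools therefore cancels out of the condition contrast. If the model has no term for that difference, it stays in the school-level residual variance, and the reported SE describes a noisier estimator than the one the design produced. With 12 to 16 schools over four conditions, an overstated SE costs power that the trial can hardly spare.

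The second issue is attrition. Once a school leaves one condition, the cancellation is no longer complete, and a model without the stratum has no means of restoring it.

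The aim-1 covariates are listed explicitly, so for the ANCOVA this is a stated choice and not a detail left to an analysis plan.

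**Working it through.** **The plan's own figure.** N:q rule: 20 participants × 9 parameters × 4 conditions = 720, or 180 per condition. This reproduces exactly. No ICC, effect size or size-outcome association enters it, so what follows rests on assumptions.

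**Inputs.** From the article: 4 conditions, 12 or 16 schools, 2 strata, blocks of four. Assumed: total SD 1 after pre-score adjustment; m = 60 students in every school; residual ICC ρ = 0.05; school size explains a share R² of residual between-school variance, with R² = 0, 0.3 or 0.5; 16 schools = 2 small and 2 large per condition; 12 schools = 2 small and 1 large per condition.

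**Step 1: which branch this is.** Design effect = 1 + 59 × 0.05 = 3.95, above 2.0. These inputs therefore describe the multilevel branch.

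**Step 2: true SD of a two-condition contrast, 16 schools, no dropout.** The variance of a school mean net of size is (1 − R²)ρ + (1 − ρ)/m, and the contrast SD is √(2 × variance / 4).
- R² = 0: 0.0500 + 0.0158 = 0.0658; SD 0.181
- R² = 0.3: 0.0350 + 0.0158 = 0.0508; SD 0.159
- R² = 0.5: 0.0250 + 0.0158 = 0.0408; SD 0.143

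With balanced strata the estimate is the same with or without the term, so this SD applies to both models.

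**Step 3: SE reported without the stratum.** The large-small difference is d = √(R²ρ/0.25). It adds 16 × 0.25 × d² / 12 = d²/3 to the residual mean square.
- R² = 0: SE 0.181
- R² = 0.3: d² = 0.06; 0.0508 + 0.0200 = 0.0708; SE 0.188, which is 18% too large
- R² = 0.5: d² = 0.10; 0.0408 + 0.0333 = 0.0742; SE 0.193, which is 35% too large

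A simulation of school means (6,000 runs per scenario) agrees:

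| R² | True SD | SE without stratum | SE with stratum | Type I error without | Type I error with |
|---|---|---|---|---|---|
| 0 | 0.181 | 0.181 | 0.181 | 4.9% | 5.1% |
| 0.3 | 0.161 | 0.188 | 0.159 | 2.6% | 5.6% |
| 0.5 | 0.146 | 0.193 | 0.143 | 1.0% | 5.2% |

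**Step 4: one large school lost from one condition.**
- 16 schools: the share of large schools in that condition falls from 1/2 to 1/3, so the shift is d/6. R² = 0.3: 0.245/6 = 0.041 SD. R² = 0.5: 0.316/6 = 0.053 SD. Simulated: 0.044 and 0.053.
- 12 schools: the share falls from 1/3 to 0, so the shift is d/3, with d = √(R²ρ/(2/9)). R² = 0.3: 0.260/3 = 0.087 SD. R² = 0.5: 0.335/3 = 0.112 SD. Simulated: 0.084 and 0.110.

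With the stratum term the simulated bias is about 0. At R² = 0 there is no shift either way.

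**Step 5: the ANCOVA branch.** With 60 students per school, a design effect of 2.0 corresponds to ρ = 1/59 = 0.017. At that upper limit:
- The shift from Step 4 becomes √(0.3 × 0.017/0.25)/6 = 0.024 SD (R² = 0.3) or 0.031 SD (R² = 0.5) with 16 schools. With 12 schools it is 0.050 or 0.065 SD.
- A student-level SE that ignores clustering is √(2/240) = 0.091. The true SD at R² = 0.3 is √(2 × (0.7 × 0.017 + 0.983/60)/4) = 0.119. Adding the stratum leaves the reported SE at √(2 × (1 − 0.3 × 0.017)/240) = 0.091. In this branch the SE is too small, and the stratum term does not change that.

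**Step 6: price of the term.** School-level residual df go from 12 − 4 = 8 to 7, or from 16 − 4 = 12 to 11. Critical t rises from 2.306 to 2.365, or from 2.179 to 2.201. The term shortens the interval once it lowers the SE by more than 2.5% (2.306/2.365 = 0.975) or 1.0% (2.179/2.201 = 0.990). In the student-level ANCOVA one df is negligible.

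**The case against.** A reader might infer that leaving out the stratum throws away the precision gained by stratifying. The documents do not support that. Step 2 shows the same true SD with and without the term while the strata are balanced; only the reported SE differs, and only if size matters beyond the pre-score. The stated purpose of stratifying was to even out student numbers, and that balance at randomisation does not depend on the model. Nothing in the article says that size is prognostic. This objection stands in full against the stronger reading. It does not remove the point, because the factor restricts the randomisation whatever the motive.

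A second objection is that the school-level degrees of freedom and SE figures do not belong to the student-level ANCOVA for which covariates are actually listed. This also stands. Steps 2 and 3 describe the multilevel alternative, whose covariates the article does not list separately. For the ANCOVA, only the possible shift after school loss carries over, at the smaller size in Step 5.

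Third, calling the size imbalance uncorrected would go too far. The pre-score absorbs any size difference already present at baseline. A shift needs a residual size effect as well as unequal loss across strata, and neither is documented. A size effect could emerge between the 7th Grade pre-measurement and the end of the second year, for example in classroom cohesion or bullying, but that is a possibility and not a finding.

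**Conclusion.** The omission is real and sits in a stated model. Its consequence is conditional. If school size predicts outcome given the pre-score, a school-level analysis without the stratum overstates the SE: by about 18% at R² = 0.3 and 35% at R² = 0.5, with 16 schools, ICC 0.05 and 60 students per school. It then tests at about 2.6% and 1.0% instead of 5%. After loss of one large school from one condition, the contrast may shift by 0 to about 0.05 SD (16 schools) or 0 to about 0.11 SD (12 schools) under the same inputs. None of R², ICC or dropout rate is in the article, so the true effect is unknown and may be nil. The conservative direction is not assured in the ANCOVA branch, where ignoring clustering can make the SE too small. That is a separate weakness of the 2.0 rule. Overall this is a modest, inexpensive improvement; it does not invalidate the planned comparison.

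**What to change.** Add the school-size stratum, coded as used at randomisation, as a fixed covariate in the aim-1 ANCOVA and in its multilevel alternative, and likewise in the mediator ANCOVAs; or state why it is left out.

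Cost: one sentence, no new data (size class is known for every randomised school) and one degree of freedom (8 to 7 or 12 to 11 at school level). If size turns out not to matter, the price is the slightly larger critical value in Step 6.

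The change should not be presented as a remedy for unmodelled clustering when the design effect is below 2.0.

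Adding size to the growth model should be optional, because it raises the parameter count behind the sample size. Assuming a linear model with one path each to intercept and slope, free in all four groups, the count is 36 + 8 = 44, and 44 × 20 = 880 students. With paths held equal across groups it is 38 × 20 = 760. At N = 720, 44 parameters leave 720/44 = 16.4 participants per parameter, still within the 10 to 20 range that the article cites but below the 20 it chose.
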